### Proposed primary and secondary outcome measures

The primary outcome of this trial is the number of hospitalizations per patient after one year of study enrollment. Secondary outcomes will be measures of health system utilization at 1-year (reported as all cause and disease specific) and will include the following:Calls to 911 (regardless of whether patient was transported to hospital)Visits to the participating family health team clinics and any after-hours clinicsLength of stay in hospital if admittedMortalityOverall health status assessment using the (Euroqol-5D 3L) EQ-5D-3L measured at baseline and one year after study enrollment [19, 20]Measures of intervention compliance and safety (that is completed assessments and visits and protocol violations identified by physician review of EMR)Cost-effectiveness analysis for this model of care

The family health team electronic patient record data will be linked via the health card number to province-wide administrative health datasets held at the ICES, a section 45 Prescribed Entity under Ontario’s Personal Health Information Protection Act. Health services data at ICES represent ‘transactions’ of health care utilization, such as inpatient/outpatient hospital utilization, emergency room and other ambulatory clinic visits, drug claims for patients 65 and older, claims for physician services in any setting, and others. Linkage to the ICES administrative databases requires use of the Ontario health card number for each subject; following linkage, only the unique ICES encrypted identifier will remain on the files used for analysis. Linkage will allow us to obtain a more comprehensive view of specific health system utilization than could be achieved with unlinked data. Many disease-specific codes have been validated in ICES’ databases [21–23].

Patients will be asked about health-related quality of life using the EQ-5D-3 L, [20] a validated measure of quality-adjusted life years (QALY). QALY, a preference-based utility measure, incorporates both length of life and quality of life into a single measure. To estimate QALYs, we will convert EQ-5D data collected in the study to utility score using a validated algorithm [19] so no additional data collection will be required. Health-related quality of life assessments will be performed at baseline and 1-year after study enrollment. Assessments will be performed by the community paramedics for patients enrolled in the intervention cohort and by the patients’ primary care physicians in the control cohort.

### Sample size

The proposed sample size is based on yearly hospitalization rates in Ontario of 296/100,000 for HF, [24] 632/100,000 for COPD [25] and 67/100,000 for DM [26] and 1-year mortality rates of 10% for HF, [27] 4.4% for COPD [28] and 8.2% for DM [29]. A Poisson regression with a sample of 695 (348 per group) achieves 80% power at a 0.05 significance level to detect a response rate ratio of at least 0.85 between groups (intervention and control) given a baseline rate of 1.85 and an assumed phi (over-dispersion parameter) of 1.0. The sample size was adjusted since a multiple regression of the covariate of interest on the other covariates in the Poisson regression is expected to have an R-squared of 0.05. We believe this to be sufficient power to detect a clinically relevant improvement of 15% in hospital admission rates. The proposed sample size calculation will be confirmed by using the baseline rates of admission as determined through ICES for patients enrolled in the EPIC study.

### Data collection and management

#### I. Confidentiality and security

Data regarding patient assessment and treatment is currently collected in the family health team’s EMR and is remotely accessed by health care providers (physicians, social workers, dieticians, physician assistants and nurse practitioners). CCAC and the community paramedics will be joining the patients’ circle of care and will sign confidentiality agreements to be provided with EMR access.

#### II. Data abstraction

Trained data abstractors will enter data from patients’ hospital visits into the EMR. They will be trained by the study staff and complete all the necessary privacy and confidentiality paperwork prior to beginning data abstraction. Patient data will be collected at each encounter with the community paramedic, both scheduled and unscheduled. Data from the paramedic reports and family health team EMRs will be abstracted and manually entered into the database housed at St. Michael’s Hospital on a continual basis throughout the study in real time. Outcome data (that is emergency department (ED) visits, hospital admissions, calls to 911) will be collected at study completion for each patient.

#### III. Data entry and data storage

All study data and clinical variables collected in the EMR will be stored on St. Michael’s Hospital research data servers. This server site is in compliance with Personal Health Information Privacy Act (PHIPA) guidelines. This password protected database has restricted access in compliance with the privacy and ethical practices of St. Michael’s Hospital. Access to the room, which contains the research file server, is restricted to designated persons who are employed by St. Michael’s Hospital. The database is stored electronically on this file server that is protected by a firewall, and making it inaccessible externally. Safeguards are in place to protect personal health information against loss, theft, as well as unauthorized access, disclosure, copying, use, or modification. The nature of the safeguards will vary depending on the format of the information, and the method of storage. Only co-investigators will have access to the final trial dataset on a request basis via the primary investigator.

#### IV. Privacy considerations for study intervention

Protecting the privacy of the subjects whose health information is obtained and housed by our research program is a mandatory component of conducting ethical clinical studies and is of utmost importance. This commitment is demonstrated through the adherence to and the compliance with Canada’s federal privacy law, the Personal Information Protection and Electronic Documents Act 2000 (PIPEDA - current to 24 March 2011), the Ontario privacy legislation, and PHIPA 2004 (last amendment: 2010).

### Data analysis

Clinical trials involving community-based medicine and prehospital providers are conducted in relatively uncontrolled environments. These settings can be unpredictable and pose many unique operational and analytical challenges for even the most rigorously designed clinical trials such as loss of patient follow-up and problems with data capture. To accommodate such challenges in a manner that maintains applicability to usual clinical practice yet ensures scientific integrity, study outcomes will be evaluated in two populations: an ITT or ‘safety population’ as our primary analysis and a modified intention-to-treat (MITT) or ‘efficacy population’ as a sensitivity analysis.

### Outcome analyses

The MITT or efficacy population will consist of all eligible randomized patients who met all eligibility criteria and who received the full study protocol (4 scheduled paramedic visits over a 1-year period or patients randomized to the control group who remained in the study for the full 1-year period). Furthermore, this trial is intended to target patients with chronic disease who are at high-risk for admission to hospital. However, initial patient enrollment into the study was based upon family physician estimation of patient risk; therefore there is a possibility that some patients enrolled in the study do not represent a high-risk group for hospital admission. Patients enrolled in the trial will have their risk of admission assessed based on their actual rates of admission over the previous 3 years. This information will be gathered through linkage with the ICES databases. Cut-off values for low, medium and high-risk categories will be calculated based on a review of the literature and clinical expertise. Only those patients who are determined to be high-risk will be included in the MITT analysis. Conversely, the ITT or effectiveness population includes all patients randomized regardless of their eligibility, adherence to study protocol or calculated risk of admission.

The primary analysis will be done using an ITT analysis. Baseline characteristics of patients in the intervention and control groups within each disease-specific group will be reported using descriptive statistics, mean/SD or median/IQR for continuous variables and count/percent for categorical as appropriate. Tests of significance will be performed using *t*-tests or Wilcoxon rank-sum test for continuous variables and chi-square or Fisher’s exact test (expected counts < 5) for categorical variables as appropriate. Two-sided *P*-value < 0.05 will be used to determine significant differences in baseline characteristics. These analyses are useful not only to assess the comparability of the treatment group but also to describe the sample of subjects who entered the trial. Test of normality for each variable will be determined using the Shapiro-Wilk test *P*-value < 0.05. All tests will be two-sided and carried out at a significance level at 5%.

The primary outcome, number of hospital admissions over 1 year will be compared by group using both Poisson regression and negative binomial regression analyses. The goodness of fit of both models will be evaluated using Akaike’s information criterion (AIC) statistics. If, in spite of randomization, differences in baseline characteristics are found using bivariate analytical strategies, these variables will be included in the regression model. Multiple imputation algorithms will be developed in order to determine values for any missing data points [30].

The secondary outcome measures, which are largely count measures, will be compared between control and intervention groups using similar Poisson regression and negative binomial models. The proportion of patients who die during the study period will be compared for the intervention and control groups within each disease-specific group using chi-square tests as well as a logistic regression model, adjusting for any potential confounding variables as appropriate.

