### Recruitment and randomization

Eligible patients will be contacted by their family physician and given multiple opportunities to provide their consent to participate. Enrollment will employ a modified Dillman method [17] with prepaid postage response cards. All patients will be consented using exactly the same process prior to randomization. See Additional files 3 and 4.A block stratified randomization procedure will be used to randomize eligible, consenting patients to treatment or control groups (1:1 ratio). Randomization will occur using a computer generated randomized number sequence allocated by block based on disease, using variable block sizes to avoid substantial imbalances in the number of patients assigned to each group (Figure 1) and to ensure the three disease groups are represented in the intervention or control (usual care) group. Stratification will balance differences in disease characteristics, which may influence the primary outcomes. Should patients have multiple diagnoses, patients with HF will be categorized HF regardless of the other diagnoses and patients with both COPD and DM will be categorized as COPD. Categorization is based on the prevalence of disease previously noted in a subset of patients in which the number of patients diagnosed as having HF was markedly reduced. A preliminary feasibility sample of cases from within the two family health care teams identified 548 patients: 74 COPD patients, 417 DM patients, and 31 HF patients. One patient had all 3 conditions, 17 had diabetes and HF, 1 had HF and COPD and finally 7 patients had both diabetes and COPD. Informed consent will be obtained from all patients prior to enrollment in the EPIC study. Patient recruitment will occur over a 1-year period. Based upon the preliminary feasibility sample and the sample size calculation required to detect a 15% difference in our primary outcome, this will be sufficient time to enroll the required number of patients.

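### Covariates enter the primary admissions model when a baseline significance test flags them; this makes the model depend on chance imbalance and does not select predictors such as disease stratum or prior admissions

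*Protocol article*

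**What the plan says.** All references are to the protocol article.

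- **Primary model (Outcome analyses).** Admissions over one year "will be compared by group using both Poisson regression and negative binomial regression analyses". No covariate is named.
- **Covariate rule (Outcome analyses).** If, in spite of randomisation, "differences in baseline characteristics are found using bivariate analytical strategies, these variables will be included in the regression model". This is the only covariate rule stated for the primary model.
- **Threshold (Outcome analyses, preceding paragraph).** "Two-sided *P*-value < 0.05 will be used to determine significant differences in baseline characteristics". The same paragraph says: "Baseline characteristics of patients in the intervention and control groups within each disease-specific group will be reported using descriptive statistics".
- **Stratification (Recruitment and randomization).** "Randomization will occur using a computer generated randomized number sequence allocated by block based on disease". The reason given is: "Stratification will balance differences in disease characteristics, which may influence the primary outcomes".
- **Prior admissions.** In Outcome analyses: "Patients enrolled in the trial will have their risk of admission assessed based on their actual rates of admission over the previous 3 years". The information is to come from linkage to the ICES databases. It serves to confirm that enrolled patients are high-risk (Patient population), to define the modified intention-to-treat set (Outcome analyses) and, as baseline admission rates, to check the sample size (Sample size).
- **Sample size.** The calculation allows for other covariates in the Poisson regression, with an R-squared of 0.05, but does not name them.

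**The concern.** A baseline test in a properly randomised trial asks whether the groups differ by more than chance, when chance is already known to be the only cause. The P-value carries no information on whether the variable predicts admissions, and prognosis is the property that makes a covariate worth having. The rule can therefore bring in irrelevant variables and pass over strong predictors that happen to be balanced.

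Disease shows the problem most clearly. It is balanced by stratified blocks, apart from incomplete blocks and family members assigned together, and it is constant within the disease groups in which baseline is described. A difference test would practically never select it, although the trial stratifies on it because it may affect the outcome.

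Two things are at stake. The primary model is not known until the data have been seen, and power may be lost that a prespecified model would keep at no cost.

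**Working it through.** **1. The plan's own figure.** Inputs from Sample size: rate ratio 0.85, baseline rate 1.85, phi 1.0, 80% power, R-squared 0.05. Tests are two-sided at 5% (Outcome analyses) and allocation is 1:1 (Recruitment and randomization). For a Poisson regression with a balanced binary covariate:

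N = phi × (1.960 × √4 + 0.8416 × √(2 + 2/0.85))² / (1.85 × ln(0.85)²) / (1 − 0.05)

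The numerator is (3.920 + 1.756)² = 32.22 and the denominator is 1.85 × 0.02641 = 0.04886. This gives 659.3, and 659.3 / 0.95 = 694.0, which rounds up to the stated 695. The figure reproduces.

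**2. Chance of at least one false flag.** Each test flags 5% of the time, so with m independent tests the chance is 1 − 0.95^m. The article does not give the number of variables k; 5 to 20 is an assumption.

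| k | Each tested once (m = k) | Each tested in 3 disease groups (m = 3k) |
|---|---|---|
| 5 | 23% | 54% |
| 10 | 40% | 79% |
| 20 | 64% | 95% |

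**3. Power under the rule and under a prespecified model.** Simulated negative binomial fits used N = 695, control rate 1.85, rate ratio 0.85 and randomisation balanced within disease. The disease mix is the feasibility sample after the hierarchy rule: HF 31 + 1 + 17 + 1 = 50, COPD 74 + 7 = 81, DM 417, total 548. The rule was applied to the prior 3-year admission count (rank test, P < 0.05). The prespecified model had disease stratum and log(prior count + 0.5). All heterogeneity values are assumptions, because the article gives none. In (b) to (d) the assumed HF:COPD:DM rates are 2:1.5:1. Scenarios (a) to (c) had 600 runs and (d) had 1,500.

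| Assumed patient risk | Power, rule | Power, prespecified | Mean SE, rule | Mean SE, prespecified |
|---|---|---|---|---|
| (a) essentially none (phi = 1) | 76.8% | 76.8% | 0.059 | 0.059 |
| (b) log-SD 0.5 and gamma variance 0.2, all shared with history | 48.5% | 69.5% | 0.081 | 0.065 |
| (c) log-SD 0.8 and gamma variance 0.3, all shared with history | 34.2% | 65.7% | 0.099 | 0.067 |
| (d) log-SD 0.5 shared with history; gamma variance 0.5 not shared | 44.5% | 46.8% | 0.092 | 0.088 |

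The differences are 0, 21.0, 31.5 and 2.3 points. The Monte Carlo standard error of one power figure is at most √(0.25/600) = 2.0 points, or √(0.25/1500) = 1.3 points in (d).

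- **Selection of prior admissions.** In (b) to (d) the count was flagged in 3.8% to 5.3% of trials, so the rule omitted a prognostic variable about 95% of the time.
- **Disease alone.** Against no adjustment, power went from 47.8% to 49.7% in (b), 34.3% to 35.2% in (c) and 44.3% to 45.5% in (d): 1 to 2 points.
- **Type I error at a rate ratio of 1, in order (a) to (d).** Rule 4.2%, 4.0%, 7.0%, 6.2%; unadjusted 4.2%, 4.3%, 8.2%, 6.1%; prespecified 4.0%, 5.8%, 6.0%, 6.3%.

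**4. Sensitivity to persistence and rate.** A second simulation used robust Poisson fits, N = 696 and assumed lognormal frailty variance 0.5. The gain in effective sample size from prespecified adjustment over no adjustment, at rate 1.85, was 47–61% with fully persistent risk, 17–25% at a log-scale correlation of 0.7, 5–12% at 0.4 and 0–7% with no persistence. At an assumed rate of 0.5 it was at most 12%; with full persistence, power rose from about 24% to about 28%.

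**The case against.** The strongest reply is that this rests on silence. The article says flagged variables will be included, not that nothing else will be. The sample size section presupposes other covariates, and an article commonly leaves the full list to the protocol or analysis plan. This stands in part: a reader might infer that disease and prior admissions are definitely excluded, and the text does not establish that. It does not rescue the rule, which the article states and which selects on the wrong property whatever else the model contains.

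Four further inferences go beyond the documents or the calculations:

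- **Prior admissions serve only to define the modified intention-to-treat set.** They also confirm high risk and check the sample size.
- **The data are already linked.** Linkage is described throughout as planned.
- **A false flag is nearly certain.** The 95% figure needs 20 variables, three tests each and independence. The article does not say that a difference within one disease group triggers adjustment of the pooled model.
- **The rule inflates type I error.** It did not, relative to the unadjusted model. The 7.0% in scenario (c) sits beside 8.2% for no adjustment.

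It is also fair that the article's only dispersion value is phi = 1.0, at which nothing is lost. Against that, the plan fits a negative binomial model and expects low-, medium- and high-risk patients, so it does not itself rely on homogeneous risk.

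**Conclusion.** The concern holds for the stated selection rule. It makes the primary model depend on chance imbalance, would practically never pick up the stratification factor, and would select a prognostic prior admission rate only about 5% of the time.

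The harm is a data-dependent model and a possible loss of power. The size of that loss is uncertain: nil at phi = 1.0, about 2 points if history predicts weakly, and about 20 to 30 points at a baseline rate of 1.85 if risk is strongly persistent. It is smaller at lower admission rates. Nearly all of any gain comes from prior admissions. Disease makes up about 76% DM in the feasibility sample (417/548) and adds 1 to 2 points, so its case rests mainly on matching the analysis to the stratified design. The large gains should not be read as expected values, because they rest on assumed heterogeneity that the article does not give.

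**What to change.** Prespecify the primary model as treatment + disease stratum (HF, COPD, DM) + prior 3-year admission rate, regardless of baseline P-values. State one functional form for the prior rate; log(prior count + 0.5) is one example. Delete the rule that adds variables found to differ at baseline, and the significance tests that feed it. Keep the descriptive baseline tables.

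The cost is a change of wording in the protocol and analysis plan. No data are needed beyond the ICES linkage already planned, and the sample size stays at 695.

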### Considerations to reduce bias

Due to the intended treatment plan it is not possible to blind paramedics, clinicians or research personnel to treatment assignment. To help minimize selection bias, randomization will occur via a computer-generated random number formulation. Detection bias will be minimized through linkage to copies of province-wide administrative datasets held at ICES. Ascertainment bias will be controlled by using objective clinical outcomes that are not under the control of the paramedic or the family health care team (for example, hospital admission, length of stay, death). Attrition bias is avoided as we are using health outcomes that are routinely measured and housed as administrative data points, and using a primary intention-to-treat (ITT) analysis will minimize the potential bias due to patient withdrawal, dropout or study protocol violations. Contamination bias will be reduced as eligible patients from the same family will be assigned to the first family member’s randomly assigned treatment group. Missing data will be minimized through point of care logic and error checks, built-in data management reports run weekly and timely oversight by study staff; however, any remaining missing data will be dealt with using multiple imputation. The statistical measures of our data management system are published [18]; there is > 90% agreement in the variables of interest common to all cases with moderate or excellent kappa (0.65 to 0.87).

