### Economic analysis

Subsequent to the outcome analysis, we will conduct an economic analysis. The objective of the economic analysis will be to compare the relative costs and effects of a community paramedicine intervention with usual care. We will conduct the analysis from the perspective of the MOHLTC using data from the randomized controlled trial and ICES. Since the effectiveness outcomes are hospitalization, ED visits, primary care visits, EMS utilization and medication use, which can be expressed in monetary terms (for example, hospitalization cost), we will convert the outcomes to dollars and will analyze the costs of the two groups. Total cost for each patient includes the cost of intervention and the health care costs incurred within 1-year following randomization (as defined in the outcome measures sections). Based on initial intervention assignment, we will analyze the cost variable as a dependent variable to estimate the difference in expected health care cost with a study group as the primary independent variable in a regression model. Employing regression will allow for the adjustment of potential confounders (for example, patient characteristics).

In theory, an ordinary least squares (OLS) model produces unbiased estimates even if the data are skewed; [31] however, additional estimation methods (for example, generalized linear models [32]) and different uncertainty methods (for example, parametric and non-parametric confidence intervals) will facilitate careful investigation of the impact various assumptions have on our conclusions. In addition, we will conduct a cost-effectiveness analysis using mortality and QALY as the outcome of interest. Methods for censored cost and outcome data will be accommodated in a net benefit regression framework [33, 34].

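### Taken as written, the rule to multiply impute all missing data would reach the one-year EQ-5D of patients who died; it should be limited to patients known to be alive

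*Protocol article*

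**What the plan says.** The protocol article gives its missing-data rule twice. Under Outcome analyses: "Multiple imputation algorithms will be developed in order to determine values for any missing data points". Under Considerations to reduce bias, after a description of data-quality checks: "any remaining missing data will be dealt with using multiple imputation". Neither statement distinguishes a value that was not collected from one that cannot exist because the patient has died.

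The section on outcome measures lists as a secondary outcome the "EQ-5D-3L measured at baseline and one year after study enrollment". There is no assessment in between. Paramedics administer it in the intervention arm and primary care physicians in the control arm, so it does not come from the linked administrative data.

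The same section says of the QALY that it "incorporates both length of life and quality of life into a single measure". For its derivation it says only that "we will convert EQ-5D data collected in the study to utility score using a validated algorithm". How survival time enters is not spelled out.

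Mortality is a secondary outcome in its own right. Under Outcome analyses, "The proportion of patients who die during the study period will be compared for the intervention and control groups", by chi-square test and logistic regression. Under Economic analysis, "we will conduct a cost-effectiveness analysis using mortality and QALY as the outcome of interest", with methods for censored data in a net benefit regression.

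On drop-out, Considerations to reduce bias says: "Attrition bias is avoided as we are using health outcomes that are routinely measured". The sentence goes on to tie this to administrative data.

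**The concern.** Deaths are foreseeable here: the Sample size section cites one-year mortality of 4.4% to 10% by disease. A patient who dies before one year leaves the second EQ-5D assessment empty. Multiple imputation fills an empty cell with a draw from a model fitted to patients who were observed, here the survivors. That is reasonable for a living patient who missed an assessment. It is not reasonable for a patient who died, because there is no underlying health state to recover. On a preference-based utility scale, death conventionally has the value 0.

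The Discussion reports under 1% missingness for critical variables and outcomes in the team's other trials. If the one-year EQ-5D were nearly as complete among survivors, most of the empty cells would belong to patients who died, and the rule would act mainly on them.

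At stake is the one-year health-status comparison. Its arm means would describe a population in which nobody dies, and any effect of the intervention on survival would drop out of it. The cost-utility result would be affected too if imputed scores were carried into QALYs without regard to survival time. The statement on attrition bias gives no protection, because its ground is administrative data and the EQ-5D is not administrative.

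**Working it through.** **The plan's own figure.** The protocol states no figure for this point. Its sample size is used below to scale the deaths, so it was checked first. The Poisson-regression formula for a binary covariate with 1:1 allocation, two-sided 5%, 80% power, baseline rate 1.85, rate ratio 0.85, phi 1.0 and R-squared 0.05 is

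N = (z₀.₉₇₅·√V₀ + z₀.₈₀·√V₁)² / (1.85 × (ln 0.85)²) / (1 − 0.05), with V₀ = 4 and V₁ = 2 + 2/0.85.

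This gives 694.0 against the stated 695, so the figure reproduces. It concerns hospital admissions and does not depend on the EQ-5D.

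**Disease mix.** From the feasibility sample under Recruitment and randomization, with the protocol's hierarchy (HF first, then COPD over DM):

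- HF: 31 + 1 + 17 + 1 = 50
- COPD: 74 + 7 = 81
- DM: 417
- Total: 548

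**Expected deaths.** With one-year mortality of 10% (HF), 4.4% (COPD) and 8.2% (DM) from the Sample size section:

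(50 × 0.10 + 81 × 0.044 + 417 × 0.082) / 548 = 42.76 / 548 = 0.078.

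That is 0.078 × 348 ≈ 27 deaths per arm, or about 54 of 695.

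**Overstatement of an arm's mean one-year utility.** Let m be mortality and u the mean utility that imputation assigns to the dead. Compared with scoring death as 0, the mean rises by m × u. The documents give no utility, so u = 0.6 to 0.8 is an assumption.

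- u = 0.6: 0.078 × 0.6 = 0.047
- u = 0.8: 0.078 × 0.8 = 0.062

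Over wider ranges (mortality 4.4% to 10%, u 0.5 to 0.8) the result runs from 0.022 to 0.080.

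**Error in the treatment contrast.** This is (m_control − m_intervention) × u.

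- Equal mortality: 0
- Assumed 2-point difference: 0.02 × 0.6 = 0.012 to 0.02 × 0.8 = 0.016
- Control mortality 7.8%, u = 0.7, mortality ratio 0.85: 0.078 × 0.15 × 0.7 = 0.008
- Same, mortality ratio 0.70: 0.078 × 0.30 × 0.7 = 0.016

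**QALYs.** If survival time were ignored and deaths fell on average at mid-year, the overstatement per arm would be m × u × 0.5: 0.023 for u = 0.6 and 0.031 for u = 0.8. If QALYs stop at death, it is zero.

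**The case against.** The strongest reply is that the protocol nowhere says that a death is a missing data point, or that a patient who died receives an imputed EQ-5D. The context of both statements is narrower than their wording. One follows a list of data-capture checks. The other closes the paragraph on the primary outcome, before the secondary outcomes are taken up. The handling of deaths in a quality-of-life analysis is often left to the analysis plan, which is not shown. This stands to the extent that no one can say the dead will be imputed. It does not dispose of the point: the rule covers all missing data without qualification, and an analysis plan that excluded deaths would have to depart from it.

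A reader might infer three stronger things, which the document does not support.

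- **That QALYs are overstated.** The protocol defines the QALY as including length of life. Overstatement would require ignoring that. The methods for censored data do not settle the matter, since death is an observed event and not censoring.
- **That a mortality difference is hidden.** Mortality is a listed outcome with its own tests and is also an outcome of the cost-effectiveness analysis. The difference would be missing only from the EQ-5D comparison.
- **That the attrition statement is simply false.** Its stated ground is administrative data, and for those outcomes it is a fair argument. It needs only a limit that keeps it from being read as covering the EQ-5D.

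Two further objections stand. The shift in each arm's mean cancels in the contrast when mortality is equal, and the protocol hypothesises no mortality difference. Scoring death as 0 is also only one legitimate choice for a health-status outcome. Reporting survivors' scores beside mortality is another.

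**Conclusion.** The point holds in a limited form. The stated rule, followed literally, would reach the one-year EQ-5D of about 7.8% of patients, or 27 per arm, and would give them survivor-like scores. Mean one-year utility would then be about 0.05 to 0.06 too high in each arm, relative to death scored as 0. The comparison between arms would be off by nothing if mortality is equal and by about 0.012 to 0.016 with a 2-point difference.

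These sizes rest on an enrolled disease mix like the feasibility sample, the protocol's cited mortality rates, a survivor utility of 0.6 to 0.8, and, for the contrast, the 2-point difference. The last two are assumptions with no source in the document.

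The error is confined to the EQ-5D health-status outcome, and to QALYs only if survival time is left out of them. It does not touch the primary outcome, the sample size or the analysis of deaths. It is worth correcting because the consequence is predictable and the correction is small.

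**What to change.** 1. Restrict multiple imputation of the EQ-5D to patients known to be alive at one year whose assessment is missing.
2. For QALYs, set utility to 0 from death and accrue QALYs only up to death. The protocol collects mortality but does not name date of death among the linked items, so confirm that the date is available from linkage.
3. For the EQ-5D health-status comparison, do not impute values after death. State in advance which approach applies: death scored as 0, or survivors' scores reported alongside mortality. The second compares groups selected by survival after randomisation and should be described that way.
4. Make clear that the statement on attrition bias covers the administrative outcomes and not the EQ-5D.

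The cost is a few sentences and one check of the linked data. No new patient assessments are needed. If death is scored as 0, reported mean utilities will be lower than under imputation, by roughly the amounts shown above.
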